High blood lead level = blood lead concentration ≥ 5 micrograms per deciliter.

STATEMENT OF COMPLIANCE

The study will be conducted in accordance with the International Conference on Harmonization guidelines for Good Clinical Practice (ICH E6), the Helsinki Declaration and Code of Federal Regulations on the Protection of Human Subjects (45 CFR Part 46), and the Terms of Award. All personnel involved in the conduct of this study have completed human subjects' protection training.

TABLE OF CONTENTS

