a. Why lead exposure in children matters, particularly in LMICs. **Lead toxicity is a major global public health concern with disproportionate impact for children in SSA**. The WHO defines blood lead levels (BLLs) ≥ 5 ug/dL as high.*^[[5]](#endnote-5)^* An estimated one in three children worldwide, 90% of whom live in LMICs, have BLLs ≥ 5 ug/dL.*^[[6]](#endnote-6)^*  UW’s Institute for Health Metrics and Evaluation estimates that 2,831,801 Kenyan children have BLLs $\geq$ 5 ug/dL, with 326,521 over 10 ug/dL*.^6^* Lead is responsible for estimated 98 million lost IQ points in Africa, a cost of ~ 4% of GDP*^[[7]](#endnote-7)^ --* 2-3 times the cost of pediatric lead exposure in Europe and the USA.*^7^*

Available data demonstrate that BLLs in children living near areas with high lead in soil and house dust in LMICs can be high.*^[[8]](#endnote-8)^* A 2021 systematic review of LMIC data reports pooled median BLLs for children in SSA countries ranging from 5.3 - 8.7 ug/dL (Kenya was not included due to inadequate data availability).*^[[9]](#endnote-9)^* **For BLLs in the range of 5 - 10 ug/dL, overt poisoning signs are not present, however, these exposures have been shown to interrupt healthy brain development, and are clearly associated with cognitive deficits (IQ point loss), behavioral changes such as reduced attention span, increased risk of antisocial and aggressive behavior, and reduced educational succes**.*^[[10]](#endnote-10)^*

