**Question 1. How can we develop a Lead Risk Survey developed for parents to be understandable, acceptable, and accurate?**

Hypotheses: This is not a hypothesis driven question. We will use parent response to modify/hone the survey for understandability and acceptability. We will compare home observation to clinic based risk reporting to improve the survey.

**Question 2. Do parent participants in an intervention program (LEIP) have good recall of lead exposure source and action steps at 6 and 9 months and does it vary based on how they received messages and the initial severity of the child’s BLL? (primary outcomes) Do participant children return for BLL recheck and is there a change in their BLL at recheck at 9 months? (exploratory outcomes)**

Hypotheses: Recall of risk factors and uptake of messaging will be high in both parents receiving messages in-clinic only and at-home. Messaging uptake will be highest for dyads with higher BLL. More than half of participants will attend follow up blood level rechecks. On average, blood lead levels will decline over the follow up period.

**Question 3. What are the barriers to uptake of lead risk reduction messaging from the perspective of parents participating in LEIP (Aim 2) and key stakeholders?**

Hypotheses. Barriers to risk reduction will include lower household socioeconomic status, lower self-efficacy, and parent occupation in industries involving e-waste, and proximity of housing to lead-contaminated soil.

GENERAL OBJECTIVE

We seek to develop and implement a novel lead testing program in Nairobi.

Specific Aims

Aim 1. Adapt, pilot and refine a prototype child lead exposure risk survey and messaging protocol

Aim 2. Evaluate uptake of tailored risk reduction messaging delivered in clinic vs at home

Aim 3. Evaluate barriers at individual and structural levels

METHODS

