## **Study Design**

This study will consist of baseline cross-sectional surveys involving larger sample sizes, with prospective cohort follow-up for a subset of enrolled participants. For Aim 1, an initial pilot survey of a lead exposure risk survey and messaging protocol will be done, and for Aim 2, an implementation randomized trial delivering a lead testing program in two ways (in-clinic only versus clinic-plus at home component). We will conduct in-depth-interviews (IDIs) with a sub-set of parents, and key-informant-interviews (KIIs) of key persons/stakeholders.

The anticipated number of participants for each study aim is shown in Table 1.

| **Table 1: Summary of study aims, study design and sample size for each aim of the LEIP Study** | | | | | |
| --- | --- | --- | --- | --- | --- |
| ***Aim*** | ***Description*** | ***Design*** | ***Population*** | ***Sample size baseline*** | ***Sample size for follow-up cohort subset*** |
| Aim 1 | Pilot study of lead POC testing protocol materials | Cross-sectional baseline  Prospective cohort subset. | Air Pollutant Exposures and Brain Development in Children (ABC) Study participants | 350 parent-child pairs enrolled will have a child lead POC test done | ~20 (all with high BLL) |
| Aim 2 | Implementation trial of lead POC test program in community (clinic only vs with home component) | Cross-sectional baseline  Randomized trial with prospective cohort subset. | Parent child pairs accessing routine well child care at health facilities | 1,500 parent-child pairs enrolled will have a child lead POC test done | 100 children with high BLL (Randomized to 50 per arm) |
| Aim 3 | In-depth-interviews with parents from Aim 2  Key-informant-interviews from key persons / stakeholders | Cross-sectional  (Qualitative) | Parents participating in Aim 2 randomized trial  Key persons /stakeholders | 20 parents for in-depth-interviews (IDI)  20 key persons/ stakeholders for key-informant-interviews (KII) |  |

AIM 1

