### *Aim 1 Enrollment Visit:*

1. Enrollment data collection. Following informed consent, parents will provide locator information and will be administered a questionnaire on demographics.
2. A child lead POC test will be performed. Two drops of blood (a fingerstick sample) will be needed for the test. If the BLL is high, a confirmatory test will be done, involving 2 additional drops of blood. The POC test will be done suing a LeadCare II device or similar.

Study staff will ensure careful washing of the child’s hand with soap and water and air drying, prior to cleaning with alcohol. Using sterile technique, a microlancet and capillary tube will be used to prick the child’s finger and draw approximately 50 uL of capillary blood. This will be loaded into the LeadCare device for a near-instant reading (3 min).

***Threshold for defining high blood lead level (BLL):*** We plan to use the WHO reference level of ≥ 5 ug/dL to define children with high BLL and eligible for follow up procedures unless stakeholders suggest an alternative lower reference level be used. For children with BLLs equal to or exceeding the reference level, **a repeat confirmatory fingerstick BLL** will be conducted. This is a practice used in the United States when timely confirmation using venous sample testing using sensitive laboratory techniques is not readily available. In these cases, two POC results ≥ the reference level are used to confirm the child’s BLL is high.

1. Venous blood draw for anemia and future lead testing using sensitive techniques. For any child who has a POC test confirmed high BLL, a venous blood sample will also be collected. This will be used to check for anemia, and archived for in-laboratory batch analysis using sensitive standardized laboratory techniques. Anemia testing is important because iron deficiency can increase absorption of lead, exacerbating toxicity. In-laboratory sensitive assays are important to allow measurement of the change in BLL from enrollment. The LeadCare II assay is not designed for precise quantitative analysis and does not allow quantitation of BLLs below 3.3 ug/dL. The venous sample will be collected using standardized sterile technique by a trained pediatric phlebotomist. To reduce discomfort, we will use a topical anesthetic for the venous blood sample collection. The sample collected will be approximately 0.5-3 mL (approximately one teaspoon) from each child.

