## **Aim 2. Overview**

Parent-child pairs will be offered child lead POC testing. Pairs with a child with a high BLL will be randomized to two groups. Both groups will receive an in-clinic lead exposure risk reduction messaging protocol. One group will also receive an at-home lead exposure risk reduction messaging protocol.

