**Secondarily,** we will estimate the proportion of mothers (self-report on in-clinic surveys) and assessed homes with identified actionable targets, e.g., suspect household products, including cosmetics, chipped paint, potential occupational exposure, or other lead containing items observed using direct read instrumentation). We will describe the number and types of actionable targets identified for each participant. These data will enhance our adapted survey and messaging protocols for Aim 2. We will summarize descriptive statistics for standardized questionnaires on recall of identified risk factors, behavior change (e.g., proportions with recall of all or some factors vs. proportions with recall of some or no factors) and Risk, Ability and Attitude (e.g,, proportions with strong agreement vs. weak or no agreement). We will select questions with higher variability, and we will refine our questionnaires as appropriate for use in Aim 2.

**Aim 2 primary outcomes will be recall of risk reduction messages, and self-report risk reduction behavior. Exploratory outcomes will be uptake of the BLL re-check and change in BLL.** Balance between arms. We will compare baseline characteristics between randomization arms to evaluate balance of demographic and risk survey characteristics. We will use chi-square tests for dichotomous variables and rank sum tests or t-tests, as appropriate, for continuous variables.

**Recall of risk reduction messages and change in risk reduction behavior.** We will describe the proportion of parents with recall of all or most of their exposure factors identified on their surveys, within each arm and by child BLL. Similarly, we will describe proportions of parents self-reporting uptake of at least one of their risk reduction recommendations within arms and by BLL. We hypothesize that recall and behavior change will be moderate (e.g., greater than 50% in both arms), and that recall and behavior change will be highest for parents in the high BLL strata. Secondarily, we will explore potential differences in outcomes between arms, acknowledging that we will have limited ability to exclude small differences. Finally, we will describe the types of messaging recommendations taken up and not taken up by participants.

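### The Aim 2 hypothesis about high-BLL strata has no comparison group as worded; a continuous BLL term would state and estimate the intended gradient better

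*Protocol*

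**What the plan says.** Protocol, Operational Definitions: "High blood lead level = blood lead concentration ≥ 5 micrograms per deciliter". Aim 2, Overview: "Pairs with a child with a high BLL will be randomized to two groups". Table 1 puts the randomised cohort at 100 children, 50 per arm, all with high BLL. Aim 2, Sample Size and Power, expects 90 of them at 9 months.

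The Analysis Plan for Aim 2 (paragraph on recall of messages and change in behaviour) will describe the proportion of parents with recall "within each arm and by child BLL", and treats uptake of recommendations similarly. It then states the hypothesis that "recall and behavior change will be highest for parents in the high BLL strata". No cut inside the trial is named there.

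Study Questions and Hypotheses, Question 2, asks whether recall varies with how severe the child's BLL was at the start, and expects: "Messaging uptake will be highest for dyads with higher BLL". The re-check paragraph of the Analysis Plan likewise expects more returns among parents whose children have higher BLLs.

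The regression models in the paragraph on implementation strategy mechanisms (log binomial, or modified Poisson with robust errors) relate uptake to Risk, Attitude and Ability scores. They are not stated to cover BLL.

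**The concern.** High BLL is a defined term in this protocol and also the entry condition for randomisation. A hypothesis about the high-BLL strata of the randomised parents, read with that term, concerns everyone in the trial. The comparison that Question 2 asks for is then not specified by the sentence meant to specify it.

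The planned form matters as well. Proportions by stratum within an arm divide about 45 parents again and discard the ordering of BLL inside each stratum. Question 2 lists variation by initial severity under its primary outcomes. If the cut is left open and the strata are small, a flat result would say little, and the choice of cut could influence what is reported.

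**Working it through.** **1. The plan's own figures.** The protocol states no power for any BLL contrast, so there is none to reproduce. Its power statement is for a one-sided, within-arm test of a single proportion. At 45 per arm, power ≈ Φ[(p1 − p0)/√(p1(1 − p1)/n) − 1.645] gives 78.2% for 67% against 50% and 78.6% for 43% against 25%, close to the stated 80%. This gives no information on a BLL gradient.

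**2. The term.** Randomised implies high BLL, which means ≥ 5 ug/dL. The complement of the high stratum among randomised children is therefore empty under the current reference level. This step needs no assumption.

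**3. Size of strata.** Evaluable per arm: 90/2 = 45.

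- Median split: 45/2 = 22.5, so 22 to 23 per stratum per arm.
- Cut at 10 ug/dL, national ratio: the Literature Review gives 2,831,801 Kenyan children at or above 5 ug/dL, "with 326,521 over 10 ug/dL". 326,521/2,831,801 = 11.5%. 45 × 0.115 = 5.2 per arm, or about 10 against 80 with arms pooled.
- The local share above 10 among children at or above 5 is not given. At an assumed 20% it is 45 × 0.20 = 9 per arm. At an assumed 30% it is 13.5, about 14.

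Exact (Clopper-Pearson) 95% intervals for an observed proportion near two thirds within one stratum of one arm:

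| Basis | Observed | 95% CI |
|---|---|---|
| Cut at 10, national ratio | 3/5 | 15–95% |
| Assumed 20% share | 6/9 | 30–93% |
| Assumed 30% share | 9/14 | 35–87% |
| Median split | 15/22 | 45–86% |

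All are wide. The cut only decides how wide.

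**4. Continuous BLL against cuts.** Assumptions: BLL lognormal, fitted to the planning prevalence of 8.2% at or above 5 ug/dL and to 11.5% of those at or above 10 (geometric mean 1.82, log SD 0.725), truncated at 5. Then n = 90 with arms pooled, two-sided 0.05, a score test, and uptake linear on the logit scale in log BLL, fixed by its values at 5 and 10 ug/dL.

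| Uptake at 5 → at 10 ug/dL | Log BLL | Median split | Cut at 10 |
|---|---|---|---|
| 50% → 80% | 61% | 42% | 31% |
| 60% → 80% | 33% | 26% | 15% |
| 50% → 70% | 32% | 21% | 18% |
| 55% → 67% | 15% | 11% | 10% |

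Repeat runs of the first three rows moved by a few points (59/42/31, 32/23/14 and 31/21/18), with the same ordering.

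If uptake instead steps up only at 10 ug/dL, the ordering changes. For 60% below and 80% above, power is 14% with log BLL, 8% with a median split and 20% with the cut.

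**The case against.** The strongest reply is that no reader would be misled. Question 2 and the re-check paragraph speak of severity and of higher BLL, and the plural strata points the same way. That stands. A reader might infer that the analysis is impossible or empty, and the documents do not support that: a gradient inside the trial is clearly intended.

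Second, the cut at 10 ug/dL appears nowhere in Aim 2. A reader might infer that any higher cut leaves about 5 parents per arm. That is true of one cut with one national ratio. The Literature Review reports 7% of children tested in Kibera above 10 ug/dL, and 8% and 31% at or above 10 in two Mombasa communities, so the local share could be larger. The phrase about arm and BLL can also be read as two separate breakdowns, in which case BLL strata would pool the arms.

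Third, a reader might infer that continuous BLL gives far more power. The gain depends on the shape of the relation, is modest against a median split, and becomes a loss if uptake steps up only at 10.

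Fourth, the plan is descriptive and claims no power here, and exact cut points may properly sit in a statistical analysis plan. That also stands. What remains is the use of a defined term where it cannot discriminate, and a stratified form where the regression already planned could be used.

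Fifth, Aim 1 keeps the 5 ug/dL level "unless stakeholders suggest an alternative lower reference level be used". If a lower level were adopted for Aim 2, a stratum at 5 or more would have a comparator. That is a contingency, not the current plan.

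Last, the protocol says LeadCare II is not built for precise quantitation, and the simulation includes no measurement error. But the point-of-care value is the one the parent hears, and any strata based on it would carry the same error.

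**Conclusion.** The point holds as an inexpensive improvement. The wording fault follows from the protocol's text alone: under the current definition the high-BLL strata have no comparison group, although a gradient among randomised children is meant. The imprecision of within-arm strata holds at every cut examined, from about 5 per arm (cut at 10, national ratio) to 22 or 23 (median split).

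The advantage of continuous BLL rests on an assumed lognormal distribution and a log-linear gradient. In three scenarios it gives about 31–61% power, against 21–42% for a median split and 14–31% for a cut at 10. At the shallowest gradient tried, all three lie between 10% and 15%. The change therefore makes better use of the data but does not make the question well powered, and a null result would still need to be read from its confidence interval.

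**What to change.** In the Analysis Plan for Aim 2, paragraph on recall and behaviour change:

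1. Replace the reference to high-BLL strata with higher enrolment BLL, in line with Question 2.
2. Add: the association of recall and of uptake with the enrolment point-of-care BLL told to the parent will be estimated with log2(BLL) as a continuous term, both arms pooled with a term for arm, by modified Poisson regression with robust errors; the result is a risk ratio per doubling of BLL with a 95% CI. State which of the two enrolment point-of-care results (first or confirmatory) is used.
3. Keep BLL strata as a descriptive table, with cuts fixed before outcome data are seen. This also shows whether a step is more plausible than a gradient.
4. Apply the same model to return for re-check. That paragraph already words its hypothesis as a gradient and needs only the model.

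Cost: a few sentences and no new data. The model type is already in the plan, but its use for BLL is an added analysis. It brings a log-linear assumption, with a loss of power if uptake rises only above a high level.

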Lead testing: Learning about a potential or actual pediatric lead exposure may cause parents stress. Should we identify any children who have blood lead levels above 25 ug/dL, we will provide a referral to the KNH tertiary referral hospital for specific management. Additional considerations include timeliness of providing child blood lead level information to parents, quality assurance and quality control in blood lead testing procedures. We will ensure that study staff are trained in each of these elements important for pediatric blood lead level testing.

Coercion: Despite every attempt by staff to ensure non-coercion during the informed consent and enrollment process, there is a non-negligible risk of participants feeling pressure to enroll in research studies.

Time Discomfort: Participants may experience some slight discomfort or stress because of the time taken to conduct the in-depth interviews/key informant interviews or blood lead level testing. However, these discomforts are anticipated to be minor.

Justification for randomization scheme: There is a need to identify approaches for lead exposure risk reduction in LMICs that maximize potential for **adoption and long-term sustainability**. Although a package including a home visit may be most effective, an in-clinic risk survey may be the most feasible and warrants evaluation. Our randomized design allows us to evaluate both models in similar groups of parent-child pairs, with the goal of informing policymakers on the minimum implementable package appropriate for this context.

POTENTIAL BENEFITS

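### Question 2 ties variation by delivery mode and BLL to the primary outcomes, but only within-arm rates are powered, and the between-arm limit is far wider than small differences

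*Protocol*

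**What the plan says.** Four parts of the protocol bear on this point.

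- **Study Questions and Hypotheses, Question 2.** After asking whether recall is good, the sentence continues "does it vary based on how they received messages and the initial severity of the child’s BLL? (primary outcomes". The hypotheses beneath it are "Recall of risk factors and uptake of messaging will be high in both parents receiving messages in-clinic only and at-home" and "Messaging uptake will be highest for dyads with higher BLL". Neither states a difference between arms.
- **Potential Risks and Benefits, justification for the randomization scheme.** Both delivery models are evaluated in similar groups "with the goal of informing policymakers on the minimum implementable package appropriate for this context".
- **Aim 2 Sample Size and Power.** There are 50 per arm, with n = 90 expected at 9 months after 10% attrition. Power is given only for a one-sided comparison of the rate within an arm: 67% against 50%, and 43% against 25%.
- **Analysis Plan, Aim 2.** Recall and uptake are described within each arm and by child BLL. The expectation is more than 50% in both arms, and that "recall and behavior change will be highest for parents in the high BLL strata". The re-check paragraph confirms that 50% is also the benchmark for the primary outcomes. On the arm contrast the plan says: "Secondarily, we will explore potential differences in outcomes between arms, acknowledging that we will have limited ability to exclude small differences".

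**The concern.** The question asked, the reason for randomising and the analysis do not line up. Variation by delivery mode sits in the sentence tagged primary, and it is what a choice between two packages depends on. Yet the powered comparison sets each arm against an external 50% benchmark, which makes no use of the randomisation. The variation by BLL has a directional hypothesis but only a description across strata whose limits are not given.

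The precision statement then tells the reader that only small differences are out of reach. If both arms exceed 50%, as hypothesised, a policymaker who trusts that sentence could conclude that the home visit adds little. The data could still be compatible with a benefit of close to 20 points.

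**Working it through.** **Inputs.** From Aim 2 Sample Size and Power: 100 randomised 1:1, 10% attrition at 9 months, so 100 × 0.90 = 90 in total and 45 per arm; planning rates 50%, 67%, 25% and 43%; one-sided alpha 0.05. Assumed here, because the protocol does not give them: two-sided 5% and 80% power for the between-arm comparison, and comparator rates of 50%, 67% and 80%.

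**1. The plan's own figure.** One-sample power, variance at the observed rate, n = 45: Φ[(p1 − p0)/√(p1(1 − p1)/n) − 1.645].

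- 67% against 50%: 0.17/√(0.67 × 0.33/45) = 0.17/0.0701 = 2.425; 2.425 − 1.645 = 0.780; power 78.2%.
- 43% against 25%: 0.18/√(0.43 × 0.57/45) = 0.18/0.0738 = 2.439; 2.439 − 1.645 = 0.794; power 78.6%.

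Both are within two points of the stated 80%. With all 90 in one arm, power would be about 95% and 98%. The plan's figure is therefore a within-arm calculation at about 45 per arm.

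**2. Detectable difference between arms.** Power = Φ[(|p1 − p2| − 1.96√(2p̄(1 − p̄)/n)) / √((p1(1 − p1) + p2(1 − p2))/n)], n = 45, solved for 80%.

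Example, 50% against 78%: p̄ = 0.64; 1.96 × √(2 × 0.64 × 0.36/45) = 0.198; denominator √((0.25 + 0.1716)/45) = 0.0968; (0.280 − 0.198)/0.0968 = 0.84; power 80%.

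| Comparator | Direction | Two-sided 5% | One-sided 5% |
|---|---|---|---|
| 50% | either | 28.0 points | 25.1 points |
| 67% | up | 23.8 | 21.6 |
| 67% | down | 29.2 | 25.9 |
| 80% | up | 18.2 | 16.7 |

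With no attrition (50 per arm) the two-sided figures are 26.7, 22.8, 27.7 and 17.5, so dropout is not the cause.

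**3. Power for plausible differences, two-sided.** 50% against 60%: 16%. 50% against 70%: 49%. 67% against 77%: 18%. 67% against 87%: 62%.

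**4. What can be excluded.** The 95% half-width for a difference when both arms have rate p is 1.96√(2p(1 − p)/45):

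- p = 0.50: 1.96 × 0.1054 = 20.7 points
- p = 0.67: 1.96 × 0.0991 = 19.4 points
- p = 0.80: 1.96 × 0.0843 = 16.5 points

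If both arms were observed at 67%, the interval would run from about −19 to +19 points. To exclude a difference with 80% power when the arms are truly equal, the multiplier is 1.96 + 0.84 = 2.80. That gives 29.5 points at 50% and 27.8 at 67%.

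**5. BLL strata.** With no cut-point given, the split is an assumption. Dividing 90 children 60/30 gives a two-sided detectable difference of about 30 points from 50% and 25 up from 67%. A 72/18 split gives about 34 and 29. Cutting a continuous measurement does not help at this sample size.

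**The case against.** The strongest reply is that the tag in Question 2 classifies outcomes, not contrasts. It is paired with an exploratory tag on re-check and BLL change, and the hypothesis is that rates are high in both arms, which is what the plan powers and benchmarks. Estimating each arm against a benchmark is a legitimate choice for a small implementation trial. The arm comparison is openly called secondary and limited, and the randomisation rationale concedes that a home visit may be most effective. Much of this stands. The wording is loose rather than a powered contrast later abandoned. But the tagged sentence contains the variation clause, and disclosing a limitation does not cure one that is described as too small.

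Three stronger readings are tempting, and the document does not support them.

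- **That only single-arm rates are examined.** The plan also describes results by BLL and explores arm differences. The contrast is secondary and unpowered, not absent.
- **That the high-BLL stratum is the whole trial**, because the Operational Definitions say "High blood lead level = blood lead concentration ≥ 5 micrograms per deciliter" and only such children are randomised. The plural strata, the reference to higher BLL in Question 2, and the purposive selection in Aim 3 across varying child BLLs show that gradations within the randomised group are meant. What is missing is a cut-point, which an analysis plan not shown here could supply.
- **That a cut at 10 ug/dL would leave very few children**, from the national counts in the Literature Review. The protocol proposes no such cut. The local surveys it cites (7% of all Kibera children above 10 ug/dL; 31% and 8% of all children in two Mombasa communities at or above 10) leave that share quite uncertain.

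The detectable difference also depends on the comparator: it falls to about 18 points upward from 80%, so no single figure should be quoted without its base rate.

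**Conclusion.** The point holds as a mismatch of emphasis plus an understated limitation. Question 2 and the randomisation rationale look to variation by delivery mode (Question 2 also by BLL), while the power statement and benchmark address within-arm rates only. At 45 per arm the design detects differences of about 24 to 29 points for comparators of 50 to 67%, and about 18 points upward from 80%. Its 95% interval half-width is about 17 to 21 points. Those are not small differences.

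The figures rest on the protocol's 10% attrition, an even split of the 90, and assumed comparator rates with a two-sided 5% test. A one-sided test lowers the detectable differences by only about 1.5 to 3.5 points.

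A reader might infer that the protocol intends to declare clinic-only messaging sufficient if both arms pass 50%. It does not say so. The risk is that nothing in the text prevents that reading. The point should be corrected, but it does not undermine the trial.

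**What to change.** 1. For recall and for uptake, report the between-arm risk difference with a 95% confidence interval beside the within-arm rates, at both 3 and 9 months or at one timepoint named as primary. A two-proportion interval is enough; a model with identity link, or marginal standardisation, also works. Modified Poisson regression alone gives a risk ratio, not this difference.
2. Estimate the BLL association with continuous log baseline BLL in place of strata. Modified Poisson, already named in the Analysis Plan for the determinant scores, gives a risk ratio for this.
3. Reconcile Question 2 with Aim 2 Sample Size and Power and with the Analysis Plan on what is primary. Question 2 also names 6 and 9 months where the visits are at 3 and 9, so settle the timepoint in the same edit.
4. Replace the reference to small differences with the figures and their base rates: at 45 per arm, about 28 points from 50%, 24 up or 29 down from 67%, and 18 up from 80%, with a 95% half-width of about 17 to 21 points.
5. State that a non-significant arm difference will not be read as showing that clinic-only messaging is sufficient.

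The cost is wording and a little more analysis on data already planned, with no added participants or visits. The stated limitation becomes less favourable.
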